### Sample size calculation

This study adopted a non-inferiority clinical trial design, and the sample size was calculated by using the sample size calculation website (https://sample-size.net). Based on the decline in lung function of patients treated with bleomycin at 1 year in the literature and the improvement in pulmonary function with nintedanib,^17 28–30^ we set the decline of FVC in the placebo group as over 8%. Based on the efficacy of nintedanib in the study of pulmonary fibrosis patients,^16^ we set the decline of FVC in the nintedanib group as 4%. Using a non-inferiority cut-off value of 10%, a one-sided α value of 0.025, and the test power of 0.09, we calculate the sample size of a single group as 53. Considering the group set a 1:1 ratio in two groups and 10% of the dropout cases during the trial, at least 116 patients will need to be included (online supplemental figure 1). Moreover, we presume that no more than 10% of the enrolled MOGCT patients may be unable to continue to receive bleomycin-based chemotherapy due to the pulmonary fibrosis, we will recruit additional 10% patients (12 patients) to better conduct this trial. Therefore, we plan to include at least 128 patients in this trial.

10.1136/bmjopen-2023-074963.supp1Supplementary data

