### Objective

The primary aim of this randomised, control trial is to determine whether nintedanib can alleviate the reduction decline of forced vital capacity (FVC) in MOGCTs patients who receive BEP chemotherapy. The secondary objective is to evaluate the decline of other pulmonary function indices (forced expiratory volume in 1 s, FEV1; FVC pred%, carbon monoxide diffusion capacity, DLCO), the safety of nintedanib treatment, oncological and fertility outcomes, and QoL in MOGCTs patients.

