#### Study group assignment

After the exclusion and inclusion process, we will perform the concealed study group assignment based on the central randomisation system. An independent statistician will generate a randomisation sequence for all the eligible MOGCTs patients. The patients will be randomly allocated to either nintedanib (experimental) or placebo (control) groups. For all the MOGCT patients enrolled in this trial, a standard treatment, namely comprehensive fertility-sparing surgical staging, or radical surgical staging plus BEP chemotherapy for 3–4 cycles, in accordance with the ESMO guidelines,^5^ no matter whether they are assigned to which group. In addition to standard treatment, patients allocated to the nintedanib group will be given oral nintedanib 150 mg two times per day before the first cycle of BEP chemotherapy until 1 month after the last cycle of BEP chemotherapy. Accordingly, patients in the control group will be given an oral placebo one tablet per time, two times per day before the first cycle of BEP chemotherapy until 1 month after the last cycle of BEP chemotherapy. The nintedanib and placebo will be provided by the study team and the appearance will be the same, without identifiable labels or packaging. The patients will be requested to record the medication and return the packaging to researchers after treatment. The flow chart (figure 1) shows the simplified procedure of group allocation, interventions and outcomes assessment.

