### Data management and statistical analysis

We will use an electronic case report form to collect data, and an electronic database will be subsequently generated. All the investigators need to be authorised to access the data and will be required to maintain data confidentiality. A periodic indication to update outcomes’ information during the follow-up will also be set up. After completion of the study, data will be stored for at least 20 years at a central data drive at the Peking Union Medical College Hospital. The datasets used and/or analysed during the current study can be obtained from the principal investigator on reasonable request. Moreover, a written, signed data-sharing agreement will be required to get data access.

The variables will be described according to the distributions, namely, mean±SD (range) for normally distributed continuous variables, otherwise they are described as medians and IQRs. Counts (percentages) will be used to present discrete variables. Methods for comparisons of variables between two groups will also be determined according to the data types. For oncology outcomes, including recurrence-free survival, overall survival and disease-specific survival, we will use the Kaplan-Meier method (log-rank test). The univariate analysis will be performed to screen factors that should be subjected to multivariate analysis, and we set the cut-off p values as 0.10 in univariate analysis. The Cox regression model or logistic regression model will be conducted in multivariate analysis. SPSS (V.20.0; SPSS), GraphPad Prism (V.8.0; GraphPad Software, La Jolla, California, USA) or STATA (SE V.12, StataCorp) software will be applied to perform the statistical analysis when appropriate. We set the statistical significance cut-off as 0.05 (two-tailed p value).

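### A placebo-controlled prevention trial is framed and sized as non-inferiority with an unjustified 10% margin of unstated scale; no superiority hypothesis for FVC decline is stated or powered

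*Protocol article*

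**What the plan says.** The protocol article's Objective section gives the primary aim as to "determine whether nintedanib can alleviate the reduction decline of forced vital capacity (FVC" in patients on BEP chemotherapy, and the title speaks of prevention. Under Study group assignment, "patients in the control group will be given an oral placebo one tablet per time, two times per day", so the control is not an active treatment.

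The Sample size calculation section then states "This study adopted a non-inferiority clinical trial design". It assumes an FVC decline of over 8% on placebo and 4% on nintedanib, and continues: "Using a non-inferiority cut-off value of 10%, a one-sided α value of 0.025, and the test power of 0.09". This yields 53 per group, then 116 with a dropout allowance, then 128 after 12 more patients are added for those who cannot continue bleomycin. The section does not say whether the 10% is in absolute points or relative, does not justify it, and gives no SD.

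The Data management and statistical analysis section says that methods for two-group comparisons depend on the type of data, and adds: "We set the statistical significance cut-off as 0.05 (two-tailed p value". It names no test for FVC and does not mention non-inferiority.

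**The concern.** Non-inferiority answers the question of whether a new treatment is not unacceptably worse than a comparator of known value. Against placebo, rejecting that null shows only that the drug is not worse than no preventive treatment by more than the margin. An inert drug satisfies this, and so may a mildly harmful one. The aim asks something else: whether nintedanib reduces the decline.

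The framing also supplies the sample size. The margin, the one-sided alpha and the power are the stated inputs to the 53 per group. That number was therefore derived for a question the trial does not ask, and the plan gives no power for the question it does ask. If meeting the cut-off were reported as prevention, the claim would rest on a criterion that a drug with no effect would often meet.

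**Working it through.** **Inputs from the protocol article (Sample size calculation).** Decline 8% on placebo (the lowest value the plan assumes) and 4% on nintedanib; margin 10%; one-sided alpha 0.025 (z = 1.96); 53 per group. Power is printed as 0.09. I take 0.90 (z = 1.2816), because 0.09 cannot be meant. The SD is not in the text, and the supplemental figure is not shown.

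**Step 1: can 53 per group be reproduced?** Not directly for a mean decline, since the SD is missing. Solving for it with SD = d × √(n/2) / (1.96 + 1.2816):
- Margin plus assumed benefit, d = 10 + 4 = 14: SD = 14 × √26.5 / 3.2416 = 22.2 points.
- Margin only, no true difference, d = 10: SD = 10 × √26.5 / 3.2416 = 15.9 points.

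Read as event rates with d = 0.14 and unpooled variance, n = (0.08×0.92 + 0.04×0.96) × 3.2416² / 0.14² = 61 per group. The Farrington-Manning method gives 77. Neither is 53. The point does not depend on reproducing that figure.

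**Step 2: where the margin lies, read as absolute points.** The null boundary is a nintedanib decline of 8 + 10 = 18%, more than double the assumed placebo decline. The margin divided by the expected benefit is 10 / (8 − 4) = 2.5.

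**Step 3: chance of meeting the criterion with 53 per group.** P = Φ((10 − δ)/SE − 1.96), where SE = SD × √(2/53) and δ is the excess decline on nintedanib.

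| SD (assumed) | SE | Inert, δ = 0 | 4 points worse, δ = 4 |
|---|---|---|---|
| 10 | 1.943 | Φ(5.148 − 1.96) = 99.9% | Φ(3.089 − 1.96) = 87% |
| 15.9 | 3.085 | 90% | 49% |
| 22.2 | 4.313 | Φ(2.319 − 1.96) = 64% | Φ(1.391 − 1.96) = 28% |

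Read as event rates:
- 8% in both arms: SE = √(2×0.08×0.92/53) = 0.0527, and P = Φ(0.10/0.0527 − 1.96) = 48%.
- 12% versus 8%: SE = 0.0581, and P = Φ(0.06/0.0581 − 1.96) = 18%.

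**Step 4: power of a superiority test for the plan's own 4-point difference.** Two-sided 0.05, power = Φ(4/SE − 1.96).

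| SD (assumed) | Power, 53 per group | Power, 64 per group (all 128 evaluable) | n per group for 90% power |
|---|---|---|---|
| 6 | 93% | 96.5% | 48 |
| 8 | 73% | 81% | 85 |
| 10 | 54% | 62% | 132 |
| 22.2 | 15% | 17% | 648 |

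With 53 evaluable per group, 90% power needs SD ≤ 4 × √26.5 / 3.2416 = 6.35 points. With all 64 per group evaluable, the limit is 4 × √32 / 3.2416 = 6.98 points.

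**The case against.** The strongest defence is that the analysis section may already lead to the right test. A two-group comparison of FVC at a two-tailed 0.05 would be an ordinary difference test, with 2.5% error in the direction of benefit. That equals the one-sided 0.025 of the sample-size section, so the two alpha figures do not conflict by themselves. The article also condenses a plan that is not shown.

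This defence limits what can be said. A reader might infer that the aim is never tested, that the plan holds two competing primary hypotheses, or that the error rate for a benefit claim is uncontrolled. The documents do not support these readings. The 0.05 rule is general and not tied to FVC, and nothing says that a claim of benefit will rest on the margin. What stands is that the protocol affirmatively adopts non-inferiority and sizes the trial on it. A separate analysis plan does not excuse a hypothesis the protocol itself states.

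A reader might also infer that the margin is larger than the whole placebo decline. That holds only if the 10% is in absolute points and the decline is at 8%, whereas the plan says over 8%. If the margin were relative to the placebo decline it would be 0.10 × 8 = 0.8 points, and the comparison would fall away. Non-inferiority to placebo would still not show benefit.

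Finally, the pass rates depend on assumed SDs. The event-rate reading fits poorly with a primary outcome worded as a degree of decline, so it is only a side check.

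**Conclusion.** The point holds: the stated design and its margin cannot answer the stated aim, and no superiority hypothesis for FVC decline is stated or powered. This conclusion follows from the text and needs no SD.

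Its size depends on reading the margin as 10 absolute points, on 53 evaluable per group and on the assumed SD. From SD 22.2, the value implied by 53 per group at 90% power with the expected benefit, down to SD 10, an inert drug meets the criterion in about 64% to 99.9% of trials. A drug 4 points worse does so in 28% to 87%. These are the consequences if meeting the margin is taken as success; they are not the error rate of an ordinary difference test.

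**What to change.** In the Sample size calculation section:
- Replace non-inferiority with superiority over placebo for FVC decline, at two-sided alpha 0.05. This agrees with the analysis section and keeps the same level in the direction of benefit.
- Delete the 10% margin.
- State the SD and its source.
- Restate the power that the planned number gives for 8% versus 4%, and correct the printed power of 0.09.

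The change is an amendment to one paragraph, to be made before unblinding, with no new procedures. The registry record should be aligned if it carries the same wording; its content is not shown here. The stated power will probably be less favourable. With 53 evaluable per group, 128 patients should not be presented as giving 90% power unless the SD is about 6.35 points or less. If it is larger, the sponsor has to choose between accepting the lower power openly and recruiting more patients.

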### Outcomes

#### Primary outcomes

The primary outcome of the study is the declined degree of FVC in MOGCT patients who receive BEP chemotherapy revealed by respiratory function test. The secondary outcomes are the decline of other pulmonary function indices (FEV1; FVC pred% and DLCO), the safety of nintedanib treatment, oncological and fertility outcomes, and QoL in MOGCTs patients.

The safety assessment of nintedanib is measured by patients’ vital signs, auxiliary examinations and AEs. The auxiliary examinations include blood tests (routine analysis, liver and kidney function, etc), urine and stool examinations. We will record any AE during the treatment and follow-up period. The definition and classification of AEs based on the CTCAE5.0. Treatment will be continued in case of grade 1 or tolerable grade 2 AEs, and temporary termination of treatment will be applied in case of the first occurrence of intolerable grade 2 or grade 3 AEs until recovery to grade 0–1 or grade 2 AEs. However, permanent termination of nintedanib medication will be considered on the second time of intolerable grade 2 or grade 3 AEs, no matter the previous toxicities or newly identified toxicities.

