## Discussion

At present, bleomycin-induced pulmonary fibrosis remains a severe chemotherapy AE that significantly impairs the therapeutic efficacy and QoL in MOGCT patients. It was estimated that 8% of patients who received bleomycin may develop varied degrees of pulmonary fibrosis, and nearly 2% were lethal.^29^ Although some optional chemotherapy regimens were proposed to decrease chemo toxicities in MOGCT patients, bleomycin is a crucial and irreplaceable regimen for chemotherapy in MOGCTs patients.^31 32^ Nonetheless, the role of bleomycin is more important for recurrent MOGCTs due to dissatisfactory responses to other regimens.^6 12^ Therefore, how to alleviate pulmonary fibrosis during bleomycin-containing chemotherapy in MOGCTs has always raised great concerns.

The metabolism of bleomycin in the lung is poor because of the low activity of detoxifying enzymes and bleomycin hydrolase.^8^ Hence, the accumulation of bleomycin in the lung, impairs the vascular system, resulting in the aggregation of inflammatory cells and fibroblasts into the lung tissue, which eventually leads to pulmonary fibrosis.^33^ Nonetheless, the exact mechanisms of pulmonary fibrosis development remain unclear, and the time between bleomycin medication and pulmonary fibrosis varies greatly among different patients.^34^ Routine prophylactic administration of antifibrosis drugs in patients receiving bleomycin may be practical due to the availability for early identification of high-risk patients. In several clinical trials of nintedanib in treating progressive fibrosing interstitial lung diseases or IPF, nintedanib showed a significantly lower reduction in pulmonary function.^18 35^ Furthermore, nintedanib has been showing promising therapeutic efficacy in treating fibrosis caused by bleomycin-containing chemotherapy and potential additional benefits in combination with common chemotherapy regimens in cancer patients.^18–20^ Besides, these studies showed relatively minor AEs of nintedanib, revealing the safety of medication in targeted treating patients.^35^

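### The printed power of 0.09 and the 53 per group do not follow from the stated inputs, and the article gives no SD for a primary outcome that is a degree of FVC decline

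*Protocol article*

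**What the plan says.** All of the following is in the protocol article.

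- **Objective:** the trial is to "determine whether nintedanib can alleviate the reduction decline of forced vital capacity (FVC") in patients receiving BEP chemotherapy.
- **Primary outcomes:** "The primary outcome of the study is the declined degree of FVC in MOGCT patients". No threshold is given that would turn this into a yes/no event.
- **Sample size calculation:** "This study adopted a non-inferiority clinical trial design". For placebo, "we set the decline of FVC in the placebo group as over 8" per cent. For the active arm, "we set the decline of FVC in the nintedanib group as 4" per cent. The margin is given as "Using a non-inferiority cut-off value of 10" per cent, with one-sided α of 0.025. The paragraph then gives the power and the result: "and the test power of 0.09, we calculate the sample size of a single group as 53".
- The total is raised to 116 for 10% dropout, and to 128 for a further 10% who may have to stop bleomycin. A sample size website and online supplemental figure 1 are cited. No formula and no SD appear in the text.

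**The concern.** Three things do not fit together. The printed power is far below anything a trial would plan for and cannot produce the stated number. Even with the obvious correction to 0.90, the placebo and nintedanib values in the text do not lead to 53. And the one set of round inputs close to the text that does lead to 53 treats the percentages as proportions of patients with an event, whereas the outcome is how far FVC falls.

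At stake is whether the power is known for the primary question. For a mean decline, the power of a given sample size is set by the SD of FVC change. Without it, nobody can say from the article what 128 patients can show about a 4-point difference.

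**Working it through.** **Inputs** (Sample size calculation section): placebo 8% (lower bound of the stated value), nintedanib 4%, margin 10 points, one-sided α 0.025 (z = 1.960), power 0.09 as printed (z = −1.341) or 0.90 if that was meant (z = 1.2816). The article names no formula. I assume the usual unpooled non-inferiority formula for two proportions:

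n per group = (z_α + z_power)² × [p1(1−p1) + p2(1−p2)] / D², where D = margin + expected benefit.

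At power 0.90, (1.960 + 1.2816)² = 10.507.

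**1. Reproducing 53.** Placebo 10%, nintedanib 4%: variances 0.0900 + 0.0384 = 0.1284; D = 0.10 + 0.06 = 0.16.
n = 10.507 × 0.1284 / 0.0256 = 52.7, so **53**. This is an exact match, but with a placebo value that the text does not state.

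**2. The stated 8% versus 4% at power 0.90.** Variances 0.0736 + 0.0384 = 0.1120; D = 0.10 + 0.04 = 0.14.
n = 10.507 × 0.1120 / 0.0196 = 60.04, so **61**. Pooled or mixed variances give 60.5 and 60.3, also 61.
Power at 53 per group: SE = √(0.1120/53) = 0.04597; Φ(0.14/0.04597 − 1.960) = Φ(1.086) = **86%**.

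**3. The printed power.** (1.960 − 1.341)² × 0.1120 / 0.0196 = 2.2, so **3 per group**. Without crediting the expected benefit (D = 0.10) it is 4.3, so 5.

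**4. Other routes to about 53.** Under the same formula, 8% versus 4% at 85% power gives 51.3, so 52. Placebo rates of roughly 9.4% to 10.8% against 4% give 55 down to 51. A calculation on means at 90% power gives 53 with an SD of 6.35 (superiority, 4-point difference), 15.9 (non-inferiority, no true difference) or 22.2 (non-inferiority, 4-point benefit). Each needs an input that the text does not give.

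**5. Later inflation.** 2 × 53 × 1.1 = 116.6, stated as 116; 116 × 1.1 = 127.6, so 128. These steps follow from 53, so the problem lies in the 53.

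**6. What 53 per group gives for a mean decline.** The SDs here are assumed, in percentage points. SE of the difference = SD × √(2/53) = 0.1943 × SD. Superiority power = Φ(4/SE − 1.960). Non-inferiority power with no true difference = Φ(10/SE − 1.960).

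| Assumed SD | Superiority, 4 points, two-sided 0.05 | Non-inferiority, margin 10, no true difference |
|---|---|---|
| 6.35 | 90% | above 99% |
| 8 | 73% | above 99% |
| 10 | 54% | above 99% |
| 12 | 40% | 99% (10/2.331 − 1.960 = 2.33) |

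For scale, 90% superiority power at SD 10 would need 2 × 100 × 10.507 / 16 = 131.3, so 132 per group.

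**The case against.** The best defence has four parts.

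- **The 0.09 is a misprint for 0.90.** Very likely so. It is still the printed value, and correcting it does not restore 53 at 8% versus 4%.
- **The text says over 8%, which does not exclude 10%.** This stands. Under the formula, n falls as the placebo value rises above 8%, so 61 per group and 86% power are the boundary case. What remains is that the placebo input is not fixed and 10% is never given.
- **The formula is not stated, and supplemental figure 1, which was not available here, may show the inputs and even an SD.** This stands as a limit. It cannot be said that no SD was used, only that the article text gives none. A reader might also infer that 53 can arise only from 10% versus 4%; step 4 shows otherwise.
- **The low powers belong to superiority, whereas the plan states non-inferiority.** This also stands. A reader might infer that the trial is underpowered for its stated test; on means, over the SDs shown, it is not. The low figures matter because the Objective asks whether nintedanib reduces the decline, which a non-inferiority result against placebo would not answer.

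A reader might also suspect that the 8% is really an incidence, because the Discussion says "It was estimated that 8% of patients who received bleomycin may develop varied degrees of pulmonary fibrosis" and cites reference 29, which is among the sources for the placebo assumption. The documents do not support that step. Reference 29 is one of several sources cited there, and the Sample size calculation section describes them as reporting lung function decline at 1 year and improvement with nintedanib.

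**Conclusion.** The sample size statement is wrong as written and needs correction. The printed power of 0.09 is incompatible with 53 per group. Read as 0.90, the figures 8% and 4% give 61 per group under the non-inferiority proportions formula, and 53 gives about 86% power. That shortfall is modest and is the worst case of a placebo value stated as over 8%.

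The weightier part is the effect measure. The exact match at 10% versus 4% suggests, without proving, that mean percentage declines were entered as event proportions. The article text gives no SD for a continuous outcome, so it contains no checkable power for it. For the superiority question in the Objective, power at 53 per group could lie anywhere from 90% to 40% for SDs of 6.35 to 12. That range rests on assumed SDs and on a 4-point true difference.

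**What to change.** In the Sample size calculation section and supplemental figure 1:

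1. Correct the printed power.
2. State the exact inputs and formula that produced 53, including a single placebo value.
3. Replace the proportions calculation, if that is what was used, with a two-means calculation. Take the SD of FVC change from the cited sources. Size it for the comparison the Objective requires: nintedanib better than placebo, 4-point difference, two-sided 0.05.
4. Keep 128 enrolled and report the power that results, with a short table over plausible SDs.

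The cost is one rewritten paragraph and one supplementary figure, with no extra patients. The downside is that the stated power may fall. Keeping 128 makes the statement honest but does not itself secure 90% power if the SD is well above 6.35.

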### Patient and public involvement

We established a panel of eight patients (in case of adult patients) or their guardians (children or adolescents’ patients) was established for this trial. They helped to modify the study design and improve the final study protocol during online focus group meetings. Particularly, they proposed the recommendations on patient-related outcomes including the minimally important clinical differences, methods of recruitment and the design of data collection. They will be actively involved throughout all critical stages of the trial through regular parent panel meetings. The results of the study will inform the participants or their guardians in case of children/adolescent’s participants. Moreover, the additional burden of the intervention in this clinical trial will be fully covered by the hospital. However, the charge due to standard treatment of MOGCTs should be paid by the patients themselves.

